# Effects of an exercise and sport intervention among refugees living in a Greek refugee camp on mental health, physical fitness and cardiovascular risk markers: study protocol for the SALEEM pragmatic randomized controlled trial

**DOI:** 10.1186/s13063-021-05808-2

**Published:** 2021-11-21

**Keywords:** Asylum seekers, Cardiovascular risk, Exercise, Fitness, Greece, Mental health, Physical activity, Post-traumatic stress disorders, Randomized controlled trial, Refugees, Sport

## Abstract

**Background:**

Due to ongoing political and social conflicts, the number of international refugees has been increasing. Refugees are exposed to severe mental and physical strain, as well as traumatic experiences during their flight. Therefore, the risk of psychiatric disorders is markedly increased among international refugees. International organizations have criticized the lack of early interventions as a key problem, because untreated mental disorders are often difficult to cure at a later stage. Today, exercise and sport have been successfully employed to treat a wide range of psychiatric disorders. With patients with post-traumatic stress disorders (PTSD), very limited empirical evidence exists, and studies carried out with international refugees are nearly non-existent.

**Methods:**

We intend to implement a pragmatic randomized controlled trial (RCT) with an exercise and sport intervention group (*n* = 68, 50% women) and a wait-list control group (*n* = 68, 50% women) in the Koutsochero refugee camp, located close to the city of Larissa (Greece). During the RCT, exercise and sport will be offered five times per week (60 min/session) for 10 weeks. Participants will be asked to participate in at least two sessions per week. The programme is developed according to the participants’ needs and preferences and they will be able to choose between a range of activities. PTSD symptoms will serve as primary outcome, and several secondary outcomes will be assessed. Qualitative data collection methods will be used to gain a more in-depth appraisal of the participants’ perception of the intervention programme. In the second year of study, the programme will be opened to all camp residents. A strategy will be developed how the programme can be continued after the end of the funding period, and how the programme can be scaled up beyond the borders of the Koutsochero camp.

**Discussion:**

By moving towards the primary prevention of chronic physical conditions and psychiatric disorders, a relevant contribution can be done to enhance the quality and quantity of life of refugee camp residents in Greece. Our findings may also strengthen the evidence for exercise as medicine as a holistic care option in refugee camps, by helping camp residents to adopt and maintain a physically active lifestyle.

**Trial registration:**

The study was registered prospectively on the 8 February 2021 with ISRCTN https://www.isrctn.com/ISRCTN16291983

## Background

For the first time worldwide, more people are forced to flee their home countries because of violence, hunger and misery than after the end of the Second World War [1]. Due to ongoing political and social conflicts, this upward trend is likely to continue in the future.

Often, refugees are exposed to severe mental and physical strain as well as traumatic experiences during their flight. After arrival in the destination country, many refugees spend several months or years in a refugee camp, where they are often confronted with future and existential fears due to the long drawn-out asylum process and their uncertain residence status. A sense of being trapped and a fear of deportation often results in feelings of apathy or resignation [2, 3].

Not surprisingly, therefore, international refugees have a significantly higher risk of suffering from psychiatric disorders, including post-traumatic stress disorders (PTSD), major depression, anxiety disorders and insomnia compared with the general population. Recently, Madsen et al. [4] observed that at least two in three asylum seekers in Denmark met ICD-10 criteria for PTSD. Médecins Sans Frontières [5] have therefore criticized the lack of early interventions in refugee camps as a key problem, particularly as many asylum seekers suffer from untreated mental disorders that are subsequently difficult to cure when settled in community settings in the country of destination. Despite this, little attention has been paid so far to the treatment of traumatized refugees in the field of psychiatry. In a recent article on the mental health status of Syrian refugees, Al-Rousan and colleagues [6] emphasized a need for greater efforts to improve the mental health of refugee populations. Particularly, they argued that measures should go beyond clinical therapy offerings and that a particular attention should be payed to non-clinical interventions that can promote health and individual resources [7].

Today, exercise and sport have been successfully employed to treat a wide range of psychiatric disorders and are considered essential to human well-being [8, 9]. Evidence also exists that exercise and sport have promise in the treatment of PTSD symptoms, depression and anxiety disorders. With regard to PTSD symptoms, Rosenbaum et al. [10] showed in a meta-analysis of four randomized controlled trials that exercise and sport interventions are significantly more effective in the treatment of PTSD symptoms than control conditions, including a wait-list control condition. The encouraging results from this review based on a small number of trials suggest that more controlled trials are needed to better understand the impact of exercise and sport interventions among individuals suffering from PTSD symptoms. In addition, the findings provide a strong foundation for the implementation of sport and exercise programmes in refugees, a population wherein PTSD seem to prevail and treatment is lacking, especially in refugee camps.

The United High Commissioner for Refugees (UNHCR) recognizes the potential of exercise and sport and uses it in refugee camps partly as a peace-building measure. More specifically, it is expected that exercise and sport activities can promote individual resources, strengthen physical health, prevent conflict, promote integration and improve individual well-being [11]. Despite this, the empirical basis for the effectiveness of exercise and sport-related measures is still scarce. Moreover, the focus on the reduction of PTSD symptoms in refugee camps through exercise and sport is a relatively new goal, which is primarily pursued (if at all) by non-governmental organizations (NGOs).

### Social relevance and interdisciplinarity

As mentioned above, in recent years, conflicts, terrorism and environmental disasters have had a profound impact on global development. Since post-conflict situations are likely to last longer, calls have been made for a change in the understanding of humanitarian aid. Thus, material and technical support must be complemented by public health programmes. In the planned study, we will for the first time carry out a methodologically sound exercise and sport intervention trial in a Greek refugee camp setting.

For several reasons, more empirical evidence is needed to better and more reliably document the potential of exercise and sport interventions in refugee camps. First, low levels of physical activity have been observed in several immigrant and refugee populations [12–14]. Second, individuals diagnosed with PTSD have a heightened risk of cardiovascular and metabolic diseases and osteoporosis [15–17] and show pronounced deficits in executive function [18]. Third, the few existing studies suggest that exercise, sport and physical activity interventions may have positive effects on mental health among refugee populations [19–21]. However, these studies were carried out in the countries of asylum, whereas investigations implemented in a refugee camp setting are missing. Because these are very different contexts, a new focus on refugee camp residents seems justified, especially as the UNHCR [1] highlights that 86% of all refugees live in refugee camps located in low- and middle-income countries, where resources are scarce, and where cost-effective measures are needed to reach large populations.

Currently, there is one attempt being undertaken to assess the impact of exercise training in juveniles, aged between 13 and 16 years, from an Ugandan refugee settlement [22]. Considering that this trial had a focus on a specific population (juveniles), and since a large number of refugees come to Europe through Greek refugee camps, Knappe et al. [23] implemented a pilot, one-group pre-test/post-test, study with adult male refugees living in a Greek refugee camp. Their results showed that regular participation in an 8-week exercise and sport programme has a positive impact on a variety of mental health outcomes, including PTSD symptoms, depressive symptoms, anxiety symptoms, health-related quality of life and physical fitness [23]. Nevertheless, since the limited resources did not allow the implementation of a randomized controlled trial (RCT), the promising findings of this pilot study must be interpreted with caution. Whereas it was shown that an exercise and sport intervention was feasible in a Greek refugee camp setting, the authors emphasized the need for future studies with stronger research designs. Towards this direction, the challenges researchers are faced with when carrying out an exercise and sport intervention in a Greek refugee camp were subsequently identified and described (e.g. language issues, selection bias, medical precautions, selection of intervention contents, investigator effects, dropout) [24].

In summary, people with mental illnesses in general and those with diagnosed PTSD in particular are especially vulnerable to cardiovascular and metabolic diseases primarily caused by a sedentary lifestyle. Refugee camp residents, in whom PTSD symptoms are highly prevalent, can thus be regarded as a particularly vulnerable population which often suffers from a mix of mental and physical health problems. Increasing physical activity levels and cardiorespiratory fitness may have important implications for tackling metabolic and cardiovascular disease and increasing cognitive functioning in this at-risk population, hence reducing the future burden of multiple chronic conditions among refugees. Increased physical activity and cardiorespiratory fitness may also reduce the likelihood of future depressive episodes and anxiety [25, 26]. By moving towards the primary prevention of chronic physical conditions and psychiatric disorders, a relevant contribution can be done to enhance the quality and quantity of life of refugee camp residents in Greece. Our findings may also strengthen the evidence for exercise as medicine as a holistic care option in refugee camps, by helping camp residents to adopt and maintain a physically active lifestyle.

### Purpose of the study

The main purpose of the present study is to examine with a pragmatic randomized controlled trial (RCT) the effects of a sport and exercise intervention among refugees living in a Greek refugee camp on PTSD symptoms (primary outcome). Based on the pilot study carried out by Knappe et al. [23], the hypothesis of our planned study is that a sport and exercise intervention will have a positive impact on the primary outcome of PTSD and on a series of secondary outcomes including perceived stress, depressive symptoms, anxiety, sleep complaints, health-related quality of life, pain, cardiorespiratory fitness, upper-body muscular strength, physical activity, cognitive function and cardiovascular risk markers.

In pursuing these objectives, we will take into account some of the lessons learned in Knappe et al.’s [24] pilot trial and will attempt to refine the methodology to address aspects that were not considered (for instance, the inclusion of female refugees). In doing so, a final purpose of our trial is to develop a longer-term and standardized (and sustainable) exercise and sport programme that (a) takes into account the cultural particularities of the target populations and (b) can easily be adapted and thus disseminated to other camps.

Based on the data assessed, further relevant aspects will be examined. These will address questions such as:
What is the prevalence of PTSD symptoms among refugees living in a Greek refugee camp, and how does the prevalence depend on participants’ socio-demographic background?How are PTSD symptoms associated with other mental health outcomes, cognitive functioning and cardiovascular health risk markers?How are cardiorespiratory fitness and grip strength associated with refugees’ mental health, cognitive function and cardiovascular health risk markers?How many refugees do achieve recommended levels of physical activity before the start of the intervention, and to what degree does this portion increase during the intervention phase?Are improvements in physical fitness during the course of the intervention period associated with improvements in mental health, cognitive functioning and cardiovascular health?Are there different needs and motivations with regard to sport, exercise and physical activity between male and female refugees (also considering their age)?What are risks and inhibiting factors linked to socio-cultural gender stereotypes and norms in this Greek refugee camp?

## Methods/design

### Study design

The SALEEM study is designed as a pragmatic randomized controlled trial (RCT) with an intervention group (IG) and a wait-list control group (WLCG), with a 1:1 allocation ratio between the IC and WLCG (“SALEEM” was chosen as a study name because “salim” means “healthy” or “fit” in Arabic and Urdu language, whereas “salem” has the same meaning in Farsi). Figure 1 provides an overview of the planned study design. The 33-item SPIRIT checklist was used when designing the study (see supplementary online material). The SPIRIT figure with more specific details regarding timepoints, interventions and assessments is provided as Fig. 2.

**Fig. 1 Fig1:**
[figure not shown]
Study design

**Fig. 2 Fig2:**
[figure not shown]
SPIRIT figure, providing an overview of timepoints, interventions and assessments of the planned pragmatic randomized controlled trial. *Notes.* *Wait-list control group only

This trial will be a pragmatic trial, carried out in a hosting site for refugees. The pragmatic design ensures increased external validity by replicating routine practice conditions including “real-life” settings and minimum exclusion criteria [27]. Also, a pragmatic design suggests that when therapist or participant blinding is not possible, such as in exercise or psychotherapy trials, it cannot be seen as a severe flaw because routine practice is also not blinded [28]. In particular, trials with blinded interventions cannot be considered fully pragmatic [29]. Moreover, collateral therapeutic interventions derived from treatment as usual conditions are not necessarily a bias factor in the context of pragmatic trials. Integrating a collateral intervention of this sort in a broader “complex” intervention represents what is typically seen in routine practice within a contemporary stepped collaborative care model. Accordingly, our findings from a pragmatic trial will be representative of routine practice and, thus, of increased external validity.

After an initial screening, participants will be assessed three times, at baseline (before the intervention), immediately post-intervention (after 3 months) and at follow-up (after 6 months). After the first 6-month follow-up, participants of the IG will have the choice whether they want to continue participation in the exercise/sport programme, whereas participants of the WLCG will start the 3-month intervention phase. The intervention duration is based on NICE guidelines that recommend 10–14 weeks for physical activity in adult depression treatment [30]. A further data assessment will be carried out with the WLCG to examine whether similar changes will occur as in the IG, after the WLCG has received the intervention programme. Interviews will be carried out during all intervention phases in order to continuously improve the quality of the exercise/sport programme.

The use of a CONSORT flow chart will allow detailed insights into the participant flow (Fig. 3). This includes refugees’ willingness to take part in an exercise and sport programme, reasons for non-participation, percentage of participants not fulfilling eligibility (inclusion criteria), dropout rate and reasons for dropout, as well as programme satisfaction and acceptance. Quantitative results will be supplemented by qualitative data collection methods, which will allow more in-depth appraisal of the participants’ perception of the intervention programme.

**Fig. 3 Fig3:**
[figure not shown]
Anticipated CONSORT flow chart

### Participants

Participants will be recruited from the “Koutsochero” refugee camp in the municipality of Larissa. Approximately 1500 residents live in this camp. In March 2020, 916 residents were aged from 16 to 59 years (62% men, 38% women). The population is diverse in terms of socio-demographic background. Most of the residents are from Syria (36%), Afghanistan (34%) and Iraq (14%), whereas the remaining 16% are from the Middle East or from the sub-Saharan region.

To estimate the minimal sample size, a power analysis was carried out using G*Power 3.1. Based on the pilot study of Knappe et al. [23], a weak-to-moderate effect can be expected on our primary outcome (PTSD symptoms; *f* = 0.19). However, in the pilot study, only males and a short-term intervention (8 weeks) were considered, and no longer-term follow-ups were carried out. Therefore, we do not know whether similarly strong effects would be found in women and whether similarly strong effects can be observed after a longer follow-up period. As a consequence, we have decided to use a slightly more conservative effect size estimate (*f* = 0.15). The mean difference in the primary outcome variable (immediately post) will be used as primary endpoint. With an α-error probability of 5%, a power of 0.8, three measurement timepoints (*r* = 0.5 between repeated measures) and four groups (one male and female IG and WLCG), a total number of 108 participants is needed. With an expected dropout rate of 25%, a total of 136 participants will be recruited (68 men, 68 women), with half of them being randomly assigned to the IG or WLCG. The expected dropout rate is based on our pilot study (16%) [23] and a meta-analysis in patients with major depression (15% in a more controlled/clinical setting) [31].

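### The 80% power at N = 108 belongs to a four-group by three-visit interaction, so it is not established for the declared endpoint, the IG–WLCG difference immediately post

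*Protocol article*

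**What the plan says.** The sample-size paragraph under Participants in the protocol article defines the endpoint: "The mean difference in the primary outcome variable (immediately post) will be used as primary endpoint". The next sentence gives the calculation: "With an α-error probability of 5%, a power of 0.8", three visits with a correlation of 0.5 between them, and "four groups (one male and female IG and WLCG), a total number of 108 participants is needed". With 25% dropout expected, 136 are to be recruited.

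The effect size starts from the pilot ("PTSD symptoms; *f* = 0.19") and is reduced to a "slightly more conservative effect size estimate (*f* = 0.15"). The reasons given are that the pilot enrolled only men, was short, and had no longer follow-up. Under Social relevance and interdisciplinarity, the pilot is described as a "one-group pre-test/post-test, study with adult male refugees living in a Greek refugee camp".

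Study design specifies two arms allocated 1:1. Effects of the intervention plans linear mixed models with treatment condition as a between-person predictor of change. The G*Power test used is not named.

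**The concern.** A power statement is useful only if it refers to the comparison on which the trial will be judged. Here the endpoint is a two-arm difference at one visit, while the inputs describe four groups followed over three visits. A four-group interaction asks whether four sex-by-arm time profiles are parallel. A sex difference in time course alone could make it significant, with no treatment effect.

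The effect size has a related problem. A one-group pre/post study measures change in treated people, including whatever would have happened without treatment. It cannot supply an arm-by-time effect directly, and the downward adjustment does not address this. A reader who takes the paragraph at face value will believe the trial has 80% power for a cautious estimate of the effect on its primary endpoint. The paragraph does not establish that.

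**Working it through.** **Inputs from the protocol article (Participants):** α = 0.05, power 0.80, f = 0.15 (pilot 0.19), m = 3 visits, r = 0.5, k = 4 groups, N = 108, dropout 25%, 136 recruited. **Assumptions made here:** two-sided test for the two-arm contrast; differences in SD units, because no SD or IES-R difference is given; analysed numbers of 51 per arm (136 × 0.75 = 102) to 54 per arm (108/2).

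**Step 1. Reproduce 108.** For the within-between interaction, λ = N·f²·m/(1 − r) = N × 0.0225 × 3/0.5 = 0.135N, df1 = (k − 1)(m − 1) = 6, df2 = (N − k)(m − 1) = 2(N − 4).

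- N = 104: λ = 14.04, df2 = 200, power 0.799.
- N = 108: λ = 14.58, df2 = 208, power 0.817.

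The smallest multiple of four that reaches 80% is 108, an exact match. At the same f, r and m, other tests give different totals:

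| Test | N |
|---|---|
| Interaction, 2 groups | 74 |
| Within factor, 4 groups | 76 |
| Between factor, 2 groups | 236 |
| Between factor, 4 groups | 328 |

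Of the variants tried, only the four-group, three-visit interaction gives 108.

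**Step 2. What f could mean as a difference D at post.** The document does not say, so several readings are set out.

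- (a) f is a one-group pre/post effect. Two means 0 and D have SD D/2, so D = 2f. For f = 0.15, D = 0.30 SD; for the pilot's 0.19, D = 0.38 SD. Carrying either over as an arm difference assumes no change in controls.
- (b) f is a true interaction f, the same in both sexes, with the full effect at post (sustained or post only). Then f = D/√18 and D = 0.15 × 4.243 = 0.64 SD.
- (c) f is a true interaction f, with the effect building linearly to follow-up. Then f = D_follow-up/√24, so D_follow-up = 0.15 × 4.899 = 0.735 SD, and half of that, 0.37 SD, is present at post.

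**Step 3. Power of the two-arm difference at post.** Two-sample noncentral t with noncentrality D·√(n/2). For baseline adjustment, D is divided by √(1 − r²) = √0.75 = 0.866. Example: n = 51, D = 0.30 gives 0.30 × √25.5 = 1.515 unadjusted and 1.515/0.866 = 1.749 adjusted.

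| Reading | D at post | Unadjusted, n = 51 to 54 | Adjusted, n = 51 to 54 |
|---|---|---|---|
| (a) f = 0.15 as 2f | 0.30 SD | 32–34% | 41–43% |
| (a) pilot f = 0.19 as 2f | 0.38 SD | 48–50% | 59–62% |
| (c) linear build-up | 0.37 SD | 45–47% | 56–59% |
| (b) full effect at post | 0.64 SD | 89–91% | 96–97% |

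**Step 4. Difference detectable with 80% power.** n = 51: 0.56 SD unadjusted, 0.49 SD adjusted. n = 54: 0.54 and 0.47 SD.

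**Step 5. Back to the test actually used.** A sustained arm difference of 0.30 SD is an interaction f of 0.30/√18 = 0.071, for which N = 108 gives 21% power. A sustained 0.38 SD is f = 0.090, giving 34%.

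**The case against.** The strongest reply is that the effect entered into the calculation was f = 0.15 in an interaction. Taken literally with the full effect at post, this is 0.64 SD, for which the post contrast has 89–97% power. On that reading the trial is more than adequately sized for its endpoint. This stands as arithmetic, and it rules out saying that the 80% is false. It does not rescue the paragraph, which never states 0.64 SD and presents its value as a reduction of a weak-to-moderate pilot effect. The same f with a linear build-up gives only 45–59%.

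Second, the planned mixed model tests treatment against change over the visits, which resembles an interaction more than a two-sample comparison, and using four groups rather than two raised N from 74 to 108. Both are fair. But the planned model enters treatment condition, not four sex-by-arm groups, and the endpoint named is still the post difference.

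Third, the 25% dropout is not tied to a visit, so more than 54 per arm may be present at post. Even with all 68 per arm, adjusted power at 0.30 SD is 52%.

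Fourth, the formula behind the pilot's f is not given, so 0.38 SD is one reading and not a documented figure. That is correct, and for this reason no fixed ratio between 0.15 and the pilot change can be claimed.

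**Conclusion.** The point holds in this form: the stated 80% is the power of a 6-df sex-by-arm by time interaction, and it is not established for the declared primary endpoint. The more-conservative label is also unsupported on the between-arm scale, because the reduction from 0.19 to 0.15 makes no allowance for the absent control arm.

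A reader might go further and infer that the trial is underpowered. The document does not support that. Power for the post difference spans about 32% to 97% across the readings above, and nothing in the text selects one. Power is below 80% if the pilot change is carried over or the effect builds gradually. It is above 80% if f = 0.15 is a true interaction effect fully present at post. Nor does the document say how a null result would be interpreted, so misreading one is a risk and not something the plan commits to.

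These figures rest on a two-sided 5% test, 51 to 54 analysed per arm, r = 0.5 between baseline and post, equal effects in both sexes, and SD units.

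**What to change.** Keep the recruited total of 136; Trial status reports that recruitment is complete. In the Participants section:

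1. State the assumed IG–WLCG difference immediately post, in SD or IES-R points, with its justification.
2. Replace the four-group, three-visit statement with the power of that contrast. For example: with 102 analysed, two-sided 5%, baseline-adjusted and r = 0.5 assumed, power is 80% for 0.49 SD (about 0.56 SD unadjusted), about 59% for 0.38 SD and 41% for 0.30 SD.
3. Remove the more-conservative wording, or justify it on the between-arm scale with an explicit allowance for change in controls.

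This is a correction to the text. The cost is a power statement that may read less favourably; no extra participants are needed.

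### Recruiting 136 does not secure the required 108 at the protocol's own 25% dropout: 102 would remain, and power would be about 79% against a stated 80%

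*Protocol article*

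**What the plan says.** The sample size paragraph in the Participants section gives a chain of three linked figures.

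- **Requirement.** The calculation, done in G*Power, uses these inputs: "With an α-error probability of 5%, a power of 0.8, three measurement timepoints"; the correlation between measurements, given as "three measurement timepoints (*r* = 0.5 between repeated measures"; and the effect size, for which "we have decided to use a slightly more conservative effect size estimate (*f* = 0.15". The result reads: "four groups (one male and female IG and WLCG), a total number of 108 participants is needed".
- **Dropout and recruitment.** "With an expected dropout rate of 25%, a total of 136 participants will be recruited (68 men, 68 women", half of them allocated to each arm. The Abstract and Discussion carry the same total forward as 68 per arm.
- **Support for the dropout rate.** "The expected dropout rate is based on our pilot study (16%) [23] and a meta-analysis in patients with major depression (15" per cent, the latter described as coming from a more controlled setting).

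The paragraph gives no formula for getting from 108 to 136, and it does not name the test chosen in G*Power. The Trial status section reports that recruitment was completed on 23 May 2021 but gives no number recruited.

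**The concern.** A dropout rate is a share of those recruited. A recruitment target that protects a required number of completers is therefore found by dividing that number by the retained share. Here the stated target, after the stated loss, leaves fewer participants than the stated requirement.

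Three things depend on this. The 136 is the headline sample size of the trial. The 25% is the yardstick against which readers will judge whether observed dropout stayed within plan, and the true margin is narrower. The stated power of 0.8 is also tied to a number of completers that the plan, on its own dropout assumption, does not reach.

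**Working it through.** **Inputs (all from the Participants section):** f = 0.15; α = 0.05; target power 0.80; m = 3 timepoints; r = 0.5; k = 4 groups; required N = 108; dropout d = 0.25; recruitment 136; cited dropout rates 16% and 15%.

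**Step 1. Reproduce 108.** The test is not named. The repeated-measures within–between interaction F test, computed as G*Power does, reproduces the figure:

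- λ = f² × N × m / (1 − r)
- df1 = (k − 1)(m − 1) = 3 × 2 = 6
- df2 = (N − k)(m − 1)

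The smallest N with power of at least 0.80 is 105 (power 0.804). Rounded up to a multiple of four groups this is 108. At N = 108, λ = 0.0225 × 108 × 3 / 0.5 = 14.58, df2 = 104 × 2 = 208, and power is 0.817. The 108 is therefore sound on its own terms.

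**Step 2. Reproduce 136.**

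- Multiplying: 108 × (1 + 0.25) = 135; the next multiple of four is 136. This matches.
- Dividing: 108 / (1 − 0.25) = 144. This does not match.

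Multiplication by 1.25 is thus the likely route, by inference from the result.

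**Step 3. Apply the stated dropout to the stated recruitment.**

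- Completers: 136 × 0.75 = 102, which is 108 − 102 = 6 short of the requirement.
- Recruits needed for 108 completers: 144, which is 144 − 136 = 8 more than planned.
- Dropout that 136 can absorb: 1 − 108/136 = 0.206, or 20.6%.

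The rounding in Step 1 does not close the gap. The unrounded minimum of 105 would need 105/0.75 = 140 recruits.

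**Step 4. Power at each number of completers, same test and inputs.**

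| Completers | How reached | Power |
|---|---|---|
| 102 | 136 with 25% loss | 0.790 |
| 104 | – | 0.799 |
| 105 | unrounded minimum | 0.804 |
| 108 | stated requirement | 0.817 |
| about 114 | 136 with 16% loss (114.2) | 0.84 |
| about 116 | 136 with 15% loss (115.6) | 0.85 |

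At the planned 25% dropout, power is 1.0 percentage point below the 80% target (80.0 − 79.0) and 2.7 points below the power at 108 (81.7 − 79.0).

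**The case against.** Four points can be made in the plan's defence.

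- **The miss is trivial.** Most of the gap between 102 and 108 is surplus from rounding 105 up to four equal cells. Against the design's own criterion the shortfall is 3 participants and 1 point of power. This stands, and it sets the size of the finding.
- **The margin still exceeds the evidence.** At the cited 15–16% the target leaves about 114 to 116 completers, with power of about 84% to 85%. This also stands. But the protocol chose 25% as its planning figure, and the recruitment target does not honour that choice.
- **Dropouts are not wholly lost.** The analysis sections plan linear mixed models, with full information maximum likelihood among the options for missing data. Participants who miss a later visit would then still contribute, and a count of completers overstates the loss of information. This may soften the shortfall, but it does not reconcile an allowance that was added to protect 108.
- **The route and the test are inferred.** This is true. The mismatch between 136, 25% and 108 needs neither inference; only the explanation of its cause and the power figures do.

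A reader might go further and project the pilot's 16% loss over 8 weeks forward at a constant rate to 6 months, and so infer a severe loss of power. The article does not support this. Nothing in it justifies a constant rate, its own planning figure is 25%, and the primary endpoint is set immediately after the intervention, not at 6 months. Nor are the three figures logically incompatible. What fails is the implied claim that 136 is enough.

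**Conclusion.** The point holds, and it is small. With 136 recruited and the protocol's own 25% dropout, 102 participants remain where 108 are said to be needed; 144 recruits would be required. The target of 136 covers 20.6% dropout.

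The retention arithmetic rests only on stated figures and on reading dropout as a share of those recruited. The power of about 79.0% against the stated 80% rests on two further assumptions: that the calculation was the interaction F test that reproduces 108, and that dropouts contribute nothing to the analysis. The second is pessimistic given the planned models.

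This is an error in a planning figure that should be corrected. It does not show that the trial is materially underpowered through its dropout allowance, and it has no bearing on the choice of primary analysis.

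**What to change.** Recruitment is reported complete, so a higher target is no longer practical. Keep the target of 136 and restate in the Participants section that:

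- 136 recruits cover dropout of about 20.6% if 108 are to complete; and
- at the expected 25% dropout, 102 complete, with power of about 79% on the stated assumptions.

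The sponsor should confirm the G*Power test used, so that the restated power rests on the actual calculation.

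The cost is one line of text, with no change to conduct, data or analysis. The only downside is that the stated figure becomes slightly less favourable.
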